# CoCStom trial: study protocol for a randomised trial comparing completeness of adjuvant chemotherapy after early versus late diverting stoma closure in low anterior resection for rectal cancer

**DOI:** 10.1186/s12885-015-1838-0

**Published:** 2015-11-21

**Keywords:** Early stoma closure, Completeness of adjuvant chemotherapy, Rectal cancer, Low anterior resection with total mesorectal excision

## Abstract

**Background:**

Current evidence supports a diverting stoma in patients undergoing low anterior resection with total mesorectal excision for rectal cancer as it reduces clinical severity of anastomotic leakage. However, relevant stoma morbidity after rectal cancer surgery exists and has a significant impact on quality of life. Moreover, a diverting stoma has an influence on completeness of chemotherapy but it remains unclear in which way. There is no evidence regarding optimal timing for stoma closure in relation to adjuvant chemotherapy. Two randomised controlled trials have studied early stoma closure after low anterior resection in patients with rectal cancer, one of them showing that early closure around day 8 after resection is possible without increasing morbidity.

**Methods/Design:**

CoCStom is a randomised multicentre trial comparing completeness of adjuvant chemotherapy as primary endpoint after early (8–10 days after resection, before starting adjuvant therapy) versus late (~26 weeks after resection and completion of adjuvant therapy) stoma closure in patients with locally advanced rectal cancer undergoing low anterior resection after neoadjuvant therapy. After exclusion of post-operative anastomotic leakage 257 patients from 30 German hospitals are planned to be included in order to assure a power of 80 % for the confirmatory analysis of at least 214 evaluable cases. An absolute increase of 20 % for the rate of completely administered adjuvant chemotherapy is regarded as a clinically meaningful step forward and serves as basis for sample size calculation. Quality of life, stoma-related complications, individual completeness of chemotherapy rate, percentage of patients stopping adjuvant therapy or undergoing dose modifications or delay, oncological outcomes, cumulative days of hospitalisation and number of readmissions, rate of symptomatic anastomotic leaks after stoma closure, mortality, post-operative complications and toxicity of adjuvant chemotherapy are secondary endpoints.

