### Statistical methods

#### Sample size calculation

The sample size calculation is based on the analysis of the primary endpoint, completeness of adjuvant chemotherapy. According to our recent randomised phase III trial on perioperative treatment of stage II and III rectal cancer, a total of 61.7 % (capecitabine) and 57.5 % (5-FU), respectively, started adjuvant chemotherapy, and 45.7 and 40.0 % had their scheduled cycles completed [14]. These data are consistent with the findings in other studies investigating perioperative chemo (radio)therapy in rectal cancer.

Based on this data, we assume a CoC rate of 42 % for the standard patient group with a diverting stoma during adjuvant chemotherapy. A 20 % absolute increase of CoC (42–62 %) is regarded as a clinically meaningful step forward. In order to significantly detect this difference on a type I error level of 5 % (two-sided) with a power of 80 %, a sample size of 107 is required in each arm based on the application of Fisher’s exact test. The Mantel-Haenszel procedure stratifying for centre will be used for the primary hypothesis of the trial.

Any major deviation from these CoC rate assumptions will lead to increased power, if the delta of 20 % is retained. According to the primary endpoint, the number of losses in the intention-to-treat (ITT) population should be minimal. A rate of 10–20 % of drop-outs and losses to follow-up is expected. Thus, about 260 patients should be randomised to ascertain sufficient power in the per-protocol analysis. Stratification by centre is foreseen, since centre-specific characteristics such as the quality of surgery, patient guidance with respect to chemotherapy compliance, etc. may have a major influence on important outcome parameters.

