#### Analysis variables and statistical methods

Primary analysis

The character of the primary analysis is confirmatory. The analysis is based on the ITT population using the ITT principles (dropouts and missing data will be counted as failures). For the analysis of the primary endpoint, the Mantel-Haenszel stratified test will be used. Corresponding 95 % confidence interval (CI) will be calculated for the CoC rates in both groups and for the rate difference and odds ratio (OR).Sensitivity analysis

The primary endpoint will be additionally analysed based on the per-protocol set comprising all patients with full documentation on the amount of adjuvant chemotherapy received. A multivariate analysis (logistic regression model) will be applied to account for the effect of potential prognostic factors such as for example age, performance status, location of the primary tumour, and T-stage.Secondary analysis

All secondary analyses have only exploratory character. P-values may only be used descriptively. All variables will be described at least by the number of observations, mean, standard deviation, median, minimum and maximum, or counts/percentages, as appropriate.

QoL data will be scored according to the algorithm described in the EORTC QLQ-C30 scoring manual [27]. While data on all functional and symptoms scales will be described, formal comparisons are going to focus on global QoL and symptoms related to the impact of chemotherapy and surgery on rectal cancer patients specifically (overall QoL, diarrhoea, constipation, vomitting).

In case of disease-free survival, local recurrence-free survival and distant recurrence-free survival Kaplan Meier survival curves for the groups will be presented and compared by the log rank test. Further secondary endpoints will be compared using a Wilcoxon-Mann–Whitney-U test or tests for contingency tables, as appropriate according to the type of data.

No interim analysis is planned. However, while the main statistical analysis is performed, as soon as documentation of post-operative therapy is completed in all patients at about 7 months post randomisation, a second analysis on long-term endpoints is performed about 1.5 years later.

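### The 80% power is stated for 214 evaluable cases, but the confirmatory test is an ITT analysis that counts losses as failures, and no power is given for that test

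*Protocol article*

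**What the plan says.** **Abstract, Methods/Design.** "257 patients from 30 German hospitals are planned to be included", so as to secure 80% power "for the confirmatory analysis of at least 214 evaluable cases".

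**Sample size calculation.** "we assume a CoC rate of 42 % for the standard patient group", and "A 20 % absolute increase of CoC (42–62 %) is regarded as a clinically meaningful step forward". For a two-sided 5% Fisher's exact test "with a power of 80 %, a sample size of 107 is required in each arm". The section expects 10–20% drop-outs and losses, says that losses in the ITT population should be very few, and concludes: "Thus, about 260 patients should be randomised to ascertain sufficient power in the per-protocol analysis". The section on compliance and loss to follow-up links the same 10–20% to the per-protocol analysis. The Fig. 1 legend asks for at least 128 per arm.

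**Analysis variables and statistical methods.** The confirmatory analysis is ITT with a Mantel-Haenszel test stratified by centre, and "dropouts and missing data will be counted as failures". The per-protocol analysis is listed as a sensitivity analysis.

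**Outcome measures and definitions.** Completeness of chemotherapy (CoC) is the share of randomised patients who finish every planned cycle.

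**The concern.** Inflating a sample size for losses is right when lost patients leave the denominator. In the ITT analysis defined here they stay in and score as failures. Apart from patients excluded as clearly non-eligible, everyone randomised is analysed, so the confirmatory test has no evaluable subset of 214. The abstract therefore gives a power for an analysis that the methods section does not make confirmatory, and the article nowhere gives the power of the one that it does.

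A null result will be read against the stated 80%. If losses are extra to the planning rates, the real figure could be lower. If they are already included, the real figure is higher and the reason given for randomising 257–260 does not apply to the primary test.

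The step from 214 to 257 also does not deliver 214 evaluable patients over the whole of the expected loss range.

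**Working it through.** **Inputs.** Two-sided alpha 5%, power 80%, 42% vs 62%, 107 per arm, loss 10–20%, about 260 randomised (Sample size calculation); 257 randomised and 214 evaluable (abstract); at least 128 per arm (Fig. 1 legend); losses as failures and the Mantel-Haenszel test (Analysis variables and statistical methods).

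**Step 1: reproduce 107 per arm.** Mean rate 0.52, difference D = 0.20.

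n0 = [1.96 × √(2 × 0.52 × 0.48) + 0.8416 × √(0.42 × 0.58 + 0.62 × 0.38)]² / 0.20² = (1.385 + 0.583)² / 0.04 ≈ 97.

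With continuity correction, n = (n0/4) × [1 + √(1 + 4/(n0 × D))]² ≈ 107. This matches the plan. Exact Fisher power at 107 per arm is 79.6%.

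**Step 2: from 214 to 257.**
- 214 × 1.2 = 256.8, which rounds to 257.
- To keep 214 after 20% loss: 214 / 0.8 = 267.5, so 268. At 10% loss the figure is 238, at 15% it is 252.
- Loss that 257 can absorb: 1 − 214/257 = 16.7%. For 260: 1 − 214/260 = 17.7%.
- Evaluable at 20% loss: 257 × 0.8 = 205.6, so 205 complete cases.
- Power on the evaluable set, 42% vs 62%: exact Fisher 79.6% at 107 per arm, 80.1% at 102 and 77.8% at 103 (the exact test moves in steps). Uncorrected chi-square falls from 83.9% at 107 per arm to 82.4% at 257 × 0.8. The cost is 0–2 points.

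**Step 3: ITT power at 257 if 42/62% already count losses as failures.** No dilution applies. Power is 89.2% (Fisher, 128/129) or 89.9% (uncorrected chi-square). On this reading 214 randomised patients would already have met the target.

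**Step 4: ITT power if losses are extra.** Suppose a fraction d is lost in each arm, independently of completion, and scored as failure. The rates become 0.42(1 − d) and 0.62(1 − d), and the difference 0.20(1 − d). Worked case, d = 0.20, uncorrected, 128.5 per arm: rates 0.336 and 0.496, mean 0.416;

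z = [0.16 × √128.5 − 1.96 × √(2 × 0.416 × 0.584)] / √(0.336 × 0.664 + 0.496 × 0.504) = (1.814 − 1.366) / 0.688 = 0.65, so power is 74.2%.

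| Extra loss d | Rates (%) | Fisher 128/128 | Fisher 128/129 | Chi-square, 257 | Mantel-Haenszel, uncorrected / corrected |
|---|---|---|---|---|---|
| 0 | 42.0 vs 62.0 | 87.7% | 89.2% | 89.9% | 89.7% / 87.1% |
| 10% | 37.8 vs 55.8 | 79.8% | 81.7% | 82.8% | 82.6% / 79.1% |
| 15% | 35.7 vs 52.7 | 75.0% | 77.0% | 78.7% | 78.5% / 74.9% |
| 20% | 33.6 vs 49.6 | 69.7% | 71.9% | 74.2% | 74.5% / 70.1% |

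The Mantel-Haenszel figures come from simulation at 257 with 30 equal centres and no variation in rates between centres. The continuity-corrected formula that reproduces 107 gives 79.4%, 74.8% and 69.9% at 10%, 15% and 20% loss.

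**The case against.** A reader might infer that the trial's real power is about 70%. The documents do not support that, for four reasons.

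- **The endpoint is defined over randomised patients.** The planning CoC rate is most naturally that same quantity.
- **The source figures point the same way.** Completion of 45.7% and 40.0% is reported beside 61.7% and 57.5% who started, so non-starters appear to count as non-completers already. How that source trial handled undocumented patients is not visible, so this is likely rather than settled.
- **Few ITT losses are expected.** The sample-size section separates these from the 10–20% allowance, which it ties to the per-protocol analysis. Patients reliably documented as having had no or incomplete chemotherapy stay evaluable, so stopping treatment is not in itself a loss.
- **The 70% combines unfavourable choices.** It takes the top of the loss range, losses extra to 42/62%, and a Fisher-type or continuity-corrected test.

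A reader might also infer that 257 is a sizing error that leaves the trial short. The loss allowance is a range, no sentence says that 257 was built for 20%, and 257 lies between the 238 and 268 that the range implies. That it came from 214 × 1.2 is an inference from the arithmetic.

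These points remove any claim that the trial is underpowered. They do not remove the mismatch. The abstract still calls the confirmatory analysis one of evaluable cases, the methods section still makes it ITT with losses as failures, and the article gives neither a figure for the very few ITT losses nor an ITT power.

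**Conclusion.** The point holds as a misattributed power figure and should be fixed, but it is not a threat to the design. The 80% belongs to 107 documented patients per arm. For the ITT test that decides the trial, power at 257 is about 87–90% if 42/62% are all-randomised rates, which is the better-supported reading. If they are documented-case rates with 10–20% losses added as failures, equally in both arms and unrelated to completion, power is about 79–83% at 10% loss and 70–75% at 20%. On that second reading it is below 80% by 15% loss under every test in the table. The stated figure fits the confirmatory test only near 10% extra loss.

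The evaluable count is a secondary matter: 257 does not guarantee at least 214 above 16.7% loss, and the shortfall at 20% is 214 − 205 = 9 patients.

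**What to change.** 1. State that 42% and 62% are rates among all randomised patients with losses counted as failures; if they are not, say so.
2. Restate power for the ITT Mantel-Haenszel test, over 0–20% loss unless the first answer makes dilution irrelevant, and attach any per-protocol power to the sensitivity analysis.
3. Replace the abstract's claim with: 257 randomised gives 214 evaluable at up to 16.7% loss and 205 at 20%.

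The cost is wording and, on the documented-case reading, a less favourable stated power at higher loss. No extra patients and no change to the primary analysis are required.

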**Discussion:**

The CoCStom trial aims to clarify optimal timing of stoma closure in the context of adjuvant chemotherapy. Depending on the results of the trial, patients could benefit either from early or late stoma closure in regard to long term oncological survival due to a higher rate of completeness of adjuvant chemotherapy treatment and thus better effectiveness.

**Trial registration:**

German Clinical Trials Register, DRKS00005113. Registered 28 August 2013

**Electronic supplementary material:**

The online version of this article (doi:10.1186/s12885-015-1838-0) contains supplementary material, which is available to authorized users.

## Background

Low anterior resection (LAR) is the procedure of choice for rectal cancer of the middle and lower third [1, 2]. An anastomosis performed close to the pelvic floor is associated with a relevant risk of anastomotic leakage (3–17 %), which contributes to mortality [3]. Based on level-1 evidence a diverting stoma effectively reduces the rate of symptomatic anastomotic leakage [4].

However, a diverting stoma also causes morbidity, which may affect nearly half of all patients as shown in an analysis of patients with protective stoma for distal colonic anastomosis [5]. Stoma-related morbidity includes high-output stoma, stoma prolapse, small bowel obstruction and wound infection and has been evaluated in several studies [5–7]. Moreover, a stoma may impair quality of life (QoL). The global QoL as well as the physical functioning and role scores are negatively influenced by stoma after LAR with total mesorectal excision (TME) as shown in two prospective observational longitudinal studies of 22 [8] and 24 patients [9] respectively. These scores and additionally the mental health improved 6 weeks after ileostomy closure. Contrarily, 23 patients receiving a high anterior resection without stoma had higher QoL scores postoperatively compared to preoperatively [9].

Very little evidence regarding the optimal timing for stoma closure was found despite an extensive systematic search in relevant literature databases and trial registries. Our prospective multicentre pilot study investigating the timing of stoma closure and longitudinal QoL before LAR with TME, before stoma closure and 6 months after stoma closure on 171 patients from 17 participating German surgical centres showed that this is in median performed 5.1 months after creation, with a wide range (0.6–32 months) [10].

Earlier stoma closure is feasible with low morbidity and no mortality as a pilot study demonstrated by closing the stoma 11 days after tumour resection [11]. Finally, a prospectively randomised multicentre trial with 186 patients confirmed that stoma closure on day 8, during the same hospitalisation, is possible without increase of the perioperative complication rate. In this study, which reflects the best available evidence, the overall postoperative complication rate was significantly lower in the early closure group (small bowel obstruction early vs. late: 3 vs. 16 %, *p* = 0.002 and medical complications: 5 vs. 15 %, *p* = 0.021) [6]. The hospitalisation period was also significantly shorter in the early stoma closure group (*p* = 0.013) but there was no difference in QoL (*p* = 0.566). Major drawback of this study is that there is no data on administered adjuvant chemotherapy. The only larger, albeit retrospective, study investigating stoma related complications and postoperative morbidity in 120 patients with colorectal carcinoma undergoing colorectal resections in regard to adjuvant chemotherapy showed a trend toward fewer complications (12.5 %) if stoma closure was performed early (i.e. before starting adjuvant chemotherapy) rather then during (42.9 %) or after (21.2 %) chemotherapy [7].

In contrast, an early closure of the stoma may also negatively influence the completeness of chemotherapy (CoC) due to complications like symptomatic anastomotic leakage or LAR syndrome. The latter is a well-known clinical condition occurring after deep anterior rectal resection potentially severely impairing QoL in these patients [12, 13]. This usually becomes evident during the first months after stoma reversal and may also aggravate side-effects of chemotherapy, again resulting in less patients receiving all cycles of planned chemotherapy.

Timing of diverting stoma closure in advanced rectal cancer has also not yet been adequately investigated in the setting of adjuvant chemotherapy. Moreover, no randomised studies specifically investigating the influence of CoC on overall survival (OS) in patients having undergone rectal resection for rectal cancer have yet been published. We re-analyzed the data from our phase-III study comparing 5-FU and capecitabine in the perioperative treatment of patients with stage II and III rectal cancer with regard to influence of CoC on survival [14]. CoC in this trial was associated with a significant improvement of 3-year disease free survival (DFS) as well as 5-year OS. Therefore, since adjuvant chemotherapy is considered to improve long-term survival in nodal-positive (stage III) disease and recommended as standard treatment in the German S3-guidelines [15, 16] it is suitable to consider CoC as primary endpoint in a prospective randomised clinical trial. Moreover, in order to improve the rates of completed adjuvant chemotherapy treatment in rectal cancer, it is highly patient relevant to investigate the influence of a stoma.

In conclusion, the optimal timing for stoma closure with regard to CoC remains controversial. It seems advantageous to close the stoma as early as possible, but on the other hand early closure may result in more complications which may impair the administration of all planned cycles of adjuvant chemotherapy.

## Methods/Design

### Trial design

CoCStom is an investigator-initiated prospective randomised open-label multicentre trial with two parallel study groups.

### Patient population

Patients with rectal cancer stadium UICC II-III undergoing low anterior resection with diverting stoma after neoadjuvant therapy and planned adjuvant chemotherapy will be included in the trial. A detailed overview of all eligibility criteria is given in Table 1.

**Table 1 Tab1:** Inclusion and exclusion criteria

Inclusion criteria	Exclusion criteria
▪ Temporary diverting stoma (independent from the stoma type)	▪ ASA >3
▪ Elective curative LAR with TME (laparoscopic, open or converted) after neoadjuvant therapy (long course chemoradiation or short-term radiotherapy - 5 × 5 Gy) for UICC II-III rectal cancer	▪ Inflammatory bowel disease
▪ No anastomotic leakage (endoscopic or contrast enema assessment of the anastomosis around day 7 after LAR)	▪ Contraindication to adjuvant chemotherapy arising after rectal cancer resection [15]
▪ Indication to undergo adjuvant chemotherapy (according to current German guidelines the pre-therapeutic stage serves as basis for the adjuvant treatment decision) [15]	▪ Disease progress to UICC IV under neoadjuvant therapy
▪ Patient has given written informed consent	▪ Immunocompromised patients (HIV-positive, patients currently under chemotherapy for other diseases or patients under immunosuppressive therapy, e.g. Prednisolone >10 mg)
▪ Age ≥18 years	▪ Participation in another intervention-trial with interference of intervention and outcome of this study
▪ Patient is able to cooperate (ability of subject to understand character and individual consequences of the clinical trial)	

*HIV* human immunodeficiency virus

### Scheme of intervention

Only centres with a special focus on colorectal surgery performing at least 20 LARs per year for rectal cancer (expertise based trial) in accordance to the German guidelines (e.g. adherence to the principles of total mesorectal excision) can take part in the CoCStom trial. This corresponds to certification requirements for colorectal cancer centres of the German Cancer Society [17].

In order to minimise performance bias, LAR within the study is performed only by surgeons with a minimum experience of 20 LARs for cancer (‘life-time experience’). In addition, surgeons need to have an adequate experience in performing the investigated stoma reversal approach. The recommended minimum number of stoma closures is 10. The individual surgeon’s experience will be documented. Each study centre provides at least one surgeon meeting these requirements. Stoma closure will be performed, according to the centre standard of care, before (experimental) or after completion (standard) of adjuvant chemotherapy.

The adjuvant chemotherapy will be performed according to the S3-guidelines for colorectal cancer [15] and recent clinical evidence [14, 18, 19] using 5-fluorouracil- (5-FU) and oxaliplatin-based regimes.

### Recruitment and trial timeline

Recruitment of the patients has started in December 2013. The duration of the trial for each patient is expected to be 24 months including follow-up at 7 and 24 months after randomisation. The duration of the entire trial is expected to be 69 months (Fig. 1).

**Fig. 1 Fig1:**
[figure not shown]
Expected patient flow from screening to final analysis. Early closure group: stoma closure and first chemotherapy (CTx) will be done around 2 days and within 4 (earliest) to 12 (latest) weeks respectively after randomisation. Late closure group: first CTx will be done within 4 (earliest) to 12 (latest) weeks after randomisation; stoma closure will be done 4 weeks after end of CTx. Randomisation will be performed around day 7 after LAR (after exclusion of an anastomotic leakage). To reach the statistically calculated goal of 257 recruited patients, at least 128 patients have to be randomised into each trial arm. W: weeks, M: months, OP: operation, *: after randomisation

